### Eligibility Criteria

The following are the eligibility criteria for the study: (1) women aged ≥18 years; (2) confirmed HIV diagnosis (per the clinic’s standard); (3) active patient (ie, not withdrawn, transferred, or dismissed); (4) 2 or more previously scheduled visits 12 months before the study enrollment; and (5) nonadherence, based on 1 or more of the following criteria: missed 1 or more visits, having a viral load >20 copies/mL, or not taking HIV antiretroviral medications as prescribed.

Participants will have to confirm at the time of enrollment that they possess a working mobile phone number (to receive text messages). We will exclude women with serious psychiatric diagnoses, who are cognitively impaired or are not able to consent for themselves.

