**Secondary outcomes**								
	**Clinical outcomes**							
		Adherence to medication		Wilson 3-item self-report measure for medication adherence (self-administered) [16]		Continuous (score); range 1-100		Participant (T0, T1, and T2)
		Clinic attendance (change)		Number of missed visits 1 year before assessment (T0), between T0 and T1, and between T1 and T2		Continuous (number)		Electronic medical record
		Viral suppression		Viral load		Categorical; ≥20 copies/mL or <20 copies/mL		Electronic medical record or measured through a blood test (T0, T1, and T2)

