	**Behavioral outcomes**							
		Depressive symptoms		Patient health questionnaire-9 (self-administered) [17-19]		Continuous (score); range 0-27		Participant (T0, T1, and T2)
		Internalized stigma		HIV stigma scale (self-administered) [20,21]		Continuous (score); range 40-160		Participant (T0, T1, and T2)
		Medical mistrust		12-Item group-based medical mistrust scale (self-administered) [22,23]		Continuous (score); range 12-60		Participant (T0, T1, and T2)
		Resilience		25-item Connor-Davidson resilience scale (self-administered) [24-26]		Continuous (score); range 0-100		Participant (T0, T1, and T2)

^a^T0: baseline.

^b^T1: time 1 (3 to 4 months postbaseline).

^c^T2: time 2 (6 to 9 months postbaseline).

The qualitative component will also comprise 6 sets of key informants, where 2 to 3 participants will represent each language. The first group of key informants (KI1) will be drawn from the FG1, approximately 1 month after FG1 for each language. KI1s will be invited to be interviewed based on their interaction with the mHealth system. The second group of key informants (KI2), who will be sampled from the intervention group, will be interviewed after T1. KI1 and KI2 will provide interim feedback to fine-tune the design of the mHealth system.

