### Study Outcomes

The primary and secondary outcomes are summarized in Table 1. Data will be collected either from the electronic medical record (EMR), the HIV database, or directly from the participants’ responses to questionnaires. For analysis, all outcomes (Table 1) will be reported as a change from baseline. As this is a pilot study, our intention is to determine the most sensitive measures. We will explore the data to determine the most suitable categorizations for a future study; therefore, the total scores will be reduced to categories once all data have been compiled. To report on the participant characteristics, sociodemographic data, including age, race/ethnicity, HIV or AIDS status, socioeconomic status, pregnancy status, substance use, and mental health history (past year), will be collected at T0.

Clinical outcomes (at T0, T1, and T2) that will be examined include a comparative history of self-reported medication adherence, visit attendance, and viral suppression reported as the biological marker of HIV viral load (copies/mL). Psychological and behavioral data include depressive symptoms, internalized stigma, resilience, and medical mistrust (Table 1).

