##### Exploratory Analyses

We will conduct exploratory analyses, where analysis of variance (ANOVA) models will be constructed for each outcome variable. Statistically significant baseline characteristics, mHealth usage, clinically relevant characteristics, and total instrument score will be entered as covariates. The ANOVAs will compare T1 and T2 outcomes to values at T0 by the study group. At T1 and T2, clinical and behavioral outcomes will be compared with values at T0 for both study arms.

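### Missed visits are raw counts over unequal windows (12, 3–4 and 2–6 months), so change from T0 shows a large fall in both arms without any effect

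*Protocol article*

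**What the plan says.** In Table 1 of the protocol article, the clinic attendance row (labelled as a change) is "Number of missed visits 1 year before assessment (T0), between T0 and T1, and between T1 and T2". Its variable type is a continuous number, not a rate or a proportion of scheduled visits. The table footnotes put T1 at 3 to 4 months and T2 at 6 to 9 months after baseline.

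The Study Outcomes section under Methods states: "For analysis, all outcomes (Table 1) will be reported as a change from baseline". The Exploratory Analyses section gives two comparisons. One is by group: "The ANOVAs will compare T1 and T2 outcomes to values at T0 by the study group". The other is within arm: "At T1 and T2, clinical and behavioral outcomes will be compared with values at T0 for both study arms".

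The Eligibility Criteria require nonadherence by at least one of three routes: "missed 1 or more visits, having a viral load >20 copies/mL", or not taking antiretrovirals as prescribed. Study Outcomes and Power Analysis say that the pilot should identify the most sensitive measures and estimate effect sizes.

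**The concern.** A change from baseline presumes that the baseline and follow-up values measure the same quantity. Here the T0 value accumulates misses over a year and the later values over a fraction of a year. A woman who misses visits at exactly the same rate throughout will show a fall.

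What is at stake is the pilot's own purpose. Missed visits would look highly responsive in both arms, simply because follow-up is shorter than the look-back. Effect sizes taken from the change within arm or over time would carry that artefact into the planning of the larger trial.

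**Working it through.** The article gives no expected count, rate or power figure for this outcome, so there is no stated figure to reproduce.

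**Windows** (Table 1 and its footnotes)
- T0: 12 months.
- T0–T1: 3 to 4 months.
- T1–T2: shortest 6 − 4 = 2 months, longest 9 − 3 = 6 months.

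**Apparent fall at a constant rate.** Expected follow-up count ÷ T0 count = m/12, so the fall is 1 − m/12. The baseline rate cancels.

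| Window m (months) | m/12 | Apparent fall |
|---|---|---|
| 2 (T1–T2, shortest) | 0.17 | 83% |
| 3 (T0–T1, shortest) | 0.25 | 75% |
| 4 (T0–T1, longest) | 0.33 | 67% |
| 6 (T1–T2, longest) | 0.50 | 50% |

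For example, at an assumed 2 missed visits a year, T0 = 2.0. The T0–T1 count is 0.50 to 0.67 (change −1.50 to −1.33), and the T1–T2 count is 0.33 to 1.00 (change −1.67 to −1.00).

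**T1 against T2.** With T1 at 4 months and T2 at 6, the second count is 2/4 = half the first. With T1 at 3 months and T2 at 9, it is 6/3 = twice the first. Both arise with no change in behaviour.

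**Consequence for tests.** Target Sample Size gives about 20 women per language in three languages, half of them controls, so about 30 per arm. The null simulation used 30 per arm and 20,000 replicates, with Poisson counts and gamma-Poisson counts (shape 1). It assumed 1, 2 or 3 missed visits a year and two-sided 0.05; the article states that level for baseline comparisons, and it is assumed here for change.
- Within-arm paired t test on raw counts: significant in 83–100% of trials at T1 and 54–100% at T2.
- The same test after rescaling (count × 12/m): about 5–7%.
- Between-arm t test on raw change: about 5% throughout.

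**Noise in the between-arm contrast.** For independent Poisson counts at yearly rate λ, Var(change) = λ(1 + m/12) and Var(follow-up count) = λm/12. The ratio is 1 + 12/m, whatever λ is. At 3.5 months it is 1 + 12/3.5 = 4.4 (5.0 at 3 months, 4.0 at 4 months). A given between-arm difference at T1, divided by the SD of change, is therefore smaller by a factor of √4.4 ≈ 2.1 than when divided by the SD of the T1 count. This applies if the T0 count is not also a covariate, and Exploratory Analyses does not name it as one.

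**Selection.** In the extreme case where every woman had at least one miss in the T0 year, the same simulation on the rescaled counts leaves a null fall of about 0.15 to 0.6 per year. Rescaling therefore removes the window artefact but not this one.

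**The case against.** The strongest reply is that this is one exploratory secondary outcome in a feasibility pilot. The primary outcomes are enrolment and acceptability, no success criterion rests on attendance, and the models are also specified by study group. That stands, and it limits the severity. It does not rescue the change over time or within arms, which the article plans explicitly. An analysis plan that is not shown may well specify the model, but it could cure the problem only by replacing the definition and change scale stated here.

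A second reply is that visit schedules are not constant, since the Rationale says that frequency of care depends on life stage. That is fair: the percentage falls are conditional on constant scheduling and miss rates. Changing schedules make the raw change harder to read, not easier.

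Three stronger readings are tempting, and the documents do not support them.
- **Bias between arms.** A reader might infer that variable windows bias the randomised contrast. Both arms share the same T1 and T2, and the recall of women who miss appointments (Intervention Fidelity) makes no distinction by arm. Bias would arise only if actual window lengths differed by arm. That is possible, because the Abstract ties T1 and T2 to clinic visits, but nothing shows it.
- **An absolute fall from the clinic's figures.** Recruitment Strategy gives 50 patients a week and 900 women a year: 50 × 52/900 = 2.89 visits per woman-year. These are patients seen, so nearer attended than scheduled visits, and they average over the whole clinic. At an assumed 30% missed, reading 2.89 as scheduled gives 0.87 misses a year and a null change at 3.5 months of −0.87 × (1 − 3.5/12) = −0.6. Reading it as attended gives 2.89/0.7 = 4.13 scheduled, 1.24 missed and a change of −0.88. Neither can be fixed from the article.
- **A definite size for regression to the mean.** A missed visit is one of three entry routes, and its look-back is not explicitly 12 months. Some regression is plausible, but its size cannot be determined.

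**Conclusion.** The point holds for changes from T0 within arms and over time. As defined, the missed-visit count falls by 67–75% at T1 and 50–83% at T2 in both arms with no true effect, assuming constant scheduling and miss rates. Those changes, and any effect size or sensitivity judgement based on them, are uninterpretable, and the T1 and T2 changes cannot be compared with each other.

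The between-arm contrast keeps its error rate under the null with equal windows, but it loses precision through the subtraction (variance ratio about 4.4 under independent Poisson counts at 3.5 months). It would also be exposed if window lengths differed by arm. Selection on missed visits may add to the apparent fall by an unknown amount. Severity is moderate.

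**What to change.** - Put all three windows on a common scale: missed visits per unit time or per scheduled visit, for example through a count model with a log-exposure offset.
- Compare the arms in T0–T1 and in T1–T2, adjusting for the T0 rate and language, in place of subtracting the T0 count.
- Show within-arm changes from T0 descriptively, without tests. Rescaling alone does not remove any selection effect, so this step is needed too.

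The cost is wording and slightly more analysis work. Recruitment Strategy indicates that the clinic database already holds appointments and missed appointments. One drawback is that a woman with no scheduled visit in a window has no value per scheduled visit; a rate per unit time avoids this.

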	**Behavioral outcomes**							
		Depressive symptoms		Patient health questionnaire-9 (self-administered) [17-19]		Continuous (score); range 0-27		Participant (T0, T1, and T2)
		Internalized stigma		HIV stigma scale (self-administered) [20,21]		Continuous (score); range 40-160		Participant (T0, T1, and T2)
		Medical mistrust		12-Item group-based medical mistrust scale (self-administered) [22,23]		Continuous (score); range 12-60		Participant (T0, T1, and T2)
		Resilience		25-item Connor-Davidson resilience scale (self-administered) [24-26]		Continuous (score); range 0-100		Participant (T0, T1, and T2)

^a^T0: baseline.

^b^T1: time 1 (3 to 4 months postbaseline).

^c^T2: time 2 (6 to 9 months postbaseline).

The qualitative component will also comprise 6 sets of key informants, where 2 to 3 participants will represent each language. The first group of key informants (KI1) will be drawn from the FG1, approximately 1 month after FG1 for each language. KI1s will be invited to be interviewed based on their interaction with the mHealth system. The second group of key informants (KI2), who will be sampled from the intervention group, will be interviewed after T1. KI1 and KI2 will provide interim feedback to fine-tune the design of the mHealth system.

#### Quantitative Component

##### Mobile Health Messaging System Prototype: Delivery of Text Messages

An English-version prototype of the mHealth messaging system using commercially available software for mobile texting has been designed. A basic user front end populates the system with data from an Excel (Microsoft Corp) spreadsheet, including mobile phone numbers, message types (medication reminder or behavioral messages), message frequency (weekly or daily), start/stop data, and message content. The communication is bidirectional, in that participants can respond with preselected codes (eg, *1* and *2*), responding to prompts such as “Press ‘1’ if you received this message.”

##### Mobile Health Messaging System Prototype: Privacy and Security

The system will not transmit personal health information (PHI). Exact names of clinics or terms such as “HIV” or “AIDS” will not be transmitted. The patients’ phone numbers are the only identifiers that will be stored in the system. Twilio is HIPAA, International Organization for Standardization 27001, and General Data Protection Regulation Privacy Shield compliant. Twilio is password-protected, and programmers use a two-factor authentication process to access the programming environment.

#### Connection Between the Qualitative and Quantitative Components

This is a parallel, mixed methods study, where the results from the qualitative component will inform the design of the intervention (quantitative component). As depicted in Figure 2, the qualitative and quantitative components will connect at 3 time points: before T0, at T1, and T2 (study end). FG1, KI1, and KI2 will provide insights into the messaging preference (reminder and behavioral) for the customization and refinement of the mHealth prototype and also pilot the mHealth prototype. All messaging will be piloted with focus groups by language.

**Figure 2 figure2:**
[figure not shown]
Data flow diagram for the study quantitative components (left) and the qualitative components (right).

### Intervention: Personalization of Reminders and Behavioral Messages

Text messages set for medication reminders will be customized based on timing, frequency, and exact content per participant preference. Behavioral messages address the barriers of internalized stigma, medical mistrust, and resilience at the individual/personal level. Participants will be blinded to their survey results. The baseline scores of participants (high internalized stigma, high medical mistrust, or low resilience) will determine the behavioral message content. At T0, participants will provide their customizations for the system. At T1 or T2, and any other time the participants choose, updates will be entered into the system. Behavioral messages have been adapted from the STEP-AD intervention aimed at decreasing internalized stigma and medical mistrust while improving adherence and resilience for women living with HIV. Suggested text messages will be presented to participants at FG1, conducted in the 3 different languages, to test for acceptability in the population of interest.

### Intervention Fidelity

#### Laboratory Data

If participants miss their scheduled clinical appointment, they will be asked to come to the clinic’s research wing, where a blood sample will be drawn by a clinical research staff member to obtain the viral load. Quantitative data will be collected as well. This procedure will ensure adherence to study data points T1 and T2.

#### Texting System

For the mHealth system, participants will be prompted to respond to predefined responses such as “Press ‘1’ if you received this message” and “Press ‘2’ if you would like us to call you.” Downloadable data usage logs will track messages that are opened and the participants’ responses. Periodically, participants will receive text surveys regarding the usefulness of a message immediately upon opening the message. These data will further guide messaging development and gauge intervention adherence.

### Intervention: Concomitant Care

At the discretion of the principal investigator (PI), participants who are concurrently enrolled in another intervention with overlapping objectives may be excluded from the data analysis. The proposed intervention will supplement the standard of care provided by the hospital, as it relates to appointment reminders.

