### Assignment to Study Arms

Participants will be randomized 1:1 to 1 of the 2 treatment arms. Randomization will be stratified by language, where approximately 10 participants per language group will be enrolled in each study arm. This ensures that approximately equal numbers of participants by language groups are represented in each study arm. A randomization schedule will be created by the study statistician based on the Excel function of random number generation. The randomization schedule will be of a randomized block nature to ensure relative equality of assignment across conditions and to prevent the potential of study staff guessing the next assignment. Randomization will take place upon the completion of baseline assessments. The study group assignment will be communicated back to the study team member who consented the patient within 24 hours of enrollment.

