#### Data Management

The completed questionnaires will be stored in a secured cabinet in a locked room inside the PI’s office. Only the PI and study team members will have access to the data forms and electronic versions of the collected data. Data will be extracted from the paper surveys and entered into an HIPAA-compliant database. Deidentified data will be exported into file formats appropriate for analysis. Authorized team members will use their unique password-protected accounts to access the database. A master spreadsheet will be available to all study team members, uploaded into a *cloud* document manager, and the participant’s study ID number will be recorded. This spreadsheet will be encrypted and will be the only database that contains identifying information. All data collection forms, consent forms, and the study log will be stored for 3 years after the closure of the study. The audio and transcription files will also be stored in the *cloud* document manager.

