##### Statistical Analysis: Missing Data

For individual statistical tests, only records with complete data will be included in the analyses.

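### The PI may drop co-enrolled women from the analysis at discretion, with no masking described; this can bias the secondary between-arm comparisons and the effect sizes meant for the later trial

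*Protocol article*

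**What the plan says.** Under Intervention: Concomitant Care, the protocol article lets the PI decide, case by case, that "participants who are concurrently enrolled in another intervention with overlapping objectives may be excluded from the data analysis". The sentence does not say what counts as overlap or when the decision is made. It does not require the decision to be made without knowledge of arm or results.

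Five other places bear on how that sentence would work:

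- **Eligibility Criteria.** There are five entry conditions, a working mobile phone, and one exclusion sentence: "We will exclude women with serious psychiatric diagnoses, who are cognitively impaired or are not able to consent for themselves". Co-enrolment in another study does not appear.
- **Assignment to Study Arms.** "Randomization will take place upon the completion of baseline assessments". Afterwards, "The study group assignment will be communicated back to the study team member who consented the patient within 24 hours of enrollment".
- **Data Management.** "Only the PI and study team members will have access to the data forms and electronic versions of the collected data".
- **Intervention: Personalization of Reminders and Behavioral Messages.** The article's only blinding statement is here: "Participants will be blinded to their survey results". It concerns a woman's own scores, not arm or outcome.
- **Statistical Analysis: Missing Data.** For each test, "only records with complete data will be included in the analyses". No statement that women are analysed as randomised overrides the PI's discretion.

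Power Analysis adds that effect sizes will be estimated when the study ends.

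**The concern.** Randomisation protects the between-arm comparison only while the groups analysed are the groups randomised. Here co-enrolment does not bar entry but can remove a woman from the analysis later, by individual judgement. There are two routes to bias.

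1. **Selective use.** If whoever decides knows the arm or the results, even an unconscious tendency to exclude women whose results look anomalous will favour one arm.
2. **Good-faith use.** A woman might join another adherence programme because of her arm or because she is doing badly, for instance a control participant seeking help elsewhere. Removing such women can unbalance the arms even if the PI is entirely neutral.

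The between-arm results for medication adherence, clinic attendance, viral suppression and the behavioural scales are at stake, as are the effect sizes to be carried into a larger trial. Of the primary outcomes, the enrolment rate comes from study logs and is not exposed. The proportion of messages opened would change if intervention women were removed, but it is not a comparison between arms.

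**Working it through.** **Sample size.** Target Sample Size gives about 20 women per language, half to control: 20 × 3 = 60 in total, so 30 per arm. Assignment to Study Arms gives about 10 per language per arm: 10 × 3 = 30. The two sections agree.

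**When the rule acts.** Co-enrolled women are not screened out, and allocation follows the baseline assessments. A Phase 2 participant removed from the analysis has therefore normally been randomised already.

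**Size of the bias.** The article gives no co-enrolment rate and no effect size, so this is an illustration under assumptions:

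- 30 women per arm, normal outcome with SD 1, no true effect;
- a fraction c of women co-enrolled, unrelated to arm and outcome, with c from 5% to 30%;
- two-sided t test at 0.05 (the article states this level for baseline comparisons; it is assumed here for outcomes);
- selective use: a co-enrolled woman is dropped if she is below the mean in the experimental arm or above it in the control arm;
- 8,000 simulated trials per scenario.

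A closed form checks the simulated bias. In the experimental arm, the probability of being kept is 1 − c/2. The expected mean of those kept is c × 0.399 / (1 − c/2), where 0.399 is the standard normal density at zero. The control arm moves equally in the other direction, so

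bias = 2 × 0.399 × c / (1 − c/2).

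| Assumed c | Closed-form bias (SD) | Simulated bias (SD) | Simulated type I error | Women dropped of 60 |
|---|---|---|---|---|
| 5% | 0.0399/0.975 = 0.041 | 0.046 | 5.2% | 1.5 |
| 10% | 0.0798/0.95 = 0.084 | 0.087 | 5.9% | 3.0 |
| 20% | 0.1596/0.90 = 0.177 | 0.179 | 10.4% | 6.0 |
| 30% | 0.2394/0.85 = 0.282 | 0.281 | 16.9% | 9.0 |

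The two agree to within simulation error. If selective dropping happens in the experimental arm only, the simulated bias is about half as large: 0.045 SD at 10% and 0.143 SD at 30%.

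**Comparison rules.** With no exclusion, or with every co-enrolled woman removed regardless of arm and outcome, simulated bias is about 0 and type I error is 4.7% to 5.2%. The blanket rule costs only numbers: about 3, 6, 12 and 18 of 60 women at the four rates. That holds because co-enrolment was assumed unrelated to arm and outcome. If it is related to both, a blanket exclusion can also bias the comparison.

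**Binary outcome.** Assume 15 of 30 women are virally suppressed in each arm. Dropping 3 unsuppressed women from the experimental arm gives 15/27 = 55.6% against 50.0%. Dropping 5 gives 15/25 = 60.0%.

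**The case against.** The best defence is that this is a pilot. Its primary outcomes are feasibility and acceptability, the exposed comparisons are secondary and labelled exploratory, and no power is claimed. The discretion reaches only co-enrolled women. At 5% to 10% co-enrolment, even deliberate misuse moves the estimate by under 0.1 SD, against a standard error of √(2/30) = 0.26 SD. Definitions of overlap and of analysis sets may also stand in a full protocol or SAP that is not shown. All of this limits the severity. It does not remove the point, which rests on the discretion the article states and not on missing detail.

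A reader might infer three stronger things that the documents do not support.

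- **That the PI is known to be unblinded.** The article says assignment goes to the team member who took consent and that the PI has access to the data. It does not say the PI sees the arm, only describes nothing to prevent it. The timing of the exclusion is likewise inferred.
- **That a few deletions would shift an arm by nearly 0.2 SD.** Dropping the lowest 3 of 30 values does shift that arm's mean by 0.19 SD. But this requires the co-enrolled women to be exactly those three, with none dropped from the other arm.
- **That an eligibility criterion would close the gap.** Screening cannot catch co-enrolment that begins between T0 and T2, 6 to 9 months later. That is also the period in which arm could influence it.

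**Conclusion.** The point holds in limited form. As written, the rule permits randomised women to be removed in a way that depends on arm or outcome, and nothing in the article restrains this. The damage would fall mainly on the secondary and exploratory between-arm comparisons and on the effect sizes for the later trial.

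Its size cannot be fixed from the documents. Under selective use in both arms it is small at 5% to 10% co-enrolment and material at 20% to 30%, where type I error reaches about 10% to 17%. These figures assume about 30 women per arm, a normal outcome, and co-enrolment unrelated to arm and outcome. They describe what the rule allows, not what the PI is expected to do. The sentence should be changed, but the feasibility conclusions do not depend on it.

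**What to change.** Replace the discretionary sentence in Intervention: Concomitant Care with three provisions:

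1. Every randomised woman stays in the main analysis in her assigned arm, whether or not she is enrolled elsewhere.
2. Co-enrolment in other interventions is recorded at T0, T1 and T2 and reported by arm.
3. Any exclusion for co-enrolment is confined to a sensitivity analysis. Its definition of overlap is set in advance and applied by someone blind to arm and outcome.

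A screening question before randomisation is optional and deals only with co-enrolment already present at baseline. If it becomes an exclusion, it would come after baseline data on 54 women have been collected, and it would alter the screen-failure proportion, which is part of a primary outcome.

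The cost is a short change of text and one added data item. The downside is that overlapping programmes may slightly dilute the main estimate; the sensitivity analysis gives an indication of how much. The article reports the texting system still in design and the launch still ahead, so the change can be made before post-launch outcome data exist.
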